### Cognitive reappraisal training

#### Stimuli

After preliminary experiments, a total of 48 positive and negative emotion pictures were selected from the Chinese Affective Picture System (CAPS), which showed high internal consistencies of valence, arousal, and dominance (0.982, 0.979, and 0.980) (Bai et al., 2005). A block design will be adopted, in which each task block contains one type of CR task, with the same number of positive and negative emotion pictures with comparable arousal.

#### Task

The CR task for each participant will include 3 conditions: simple viewing (baseline), CR + (emotion upregulation), and CR- (emotion downregulation). The CR task starts with the baseline condition, and then the order of CR + and CR- tasks will be counterbalanced across the participants. The task was designed based on our previous study of the CR ability of patients diagnosed with depressive disorder (Wang et al., 2014, 2017). To motivate the participants to generate reappraisal strategies, the practice before the formal CR task will give the participants two examples that provide creative reappraisal strategies vs. objective descriptions of the emotion stimuli pictures (Wu X. et al., 2017, Wu et al., 2022) and then require the participants to reappraise each of the four emotion pictures (2 for the emotion upregulation condition and 2 for the emotion downregulation condition See details below) and type their strategies in the blank under each picture on the computer screen.

##### Simple viewing task (baseline)

The participants will be instructed to naturally view the emotion stimuli pictures in sequence and rate their emotional arousal after each picture. The following instructions will be provided at the beginning of the task: “When a fixation point ‘ + ’ appears in the center of the screen, please keep your eyes on the fixation point. When the fixation point disappears, a picture appears; please look at the picture. After the picture disappears, please evaluate your emotional intensity at this time based on the instructions provided.”

##### Cognitive reappraisal + task (emotion upregulation)

The participants will be instructed to enhance their emotions while viewing stimuli pictures and rate their emotional arousal after each picture. The following instructions will be provided at the beginning of the task: “When a fixation point ‘ + ’ appears in the center of the screen, please keep your eyes on the fixation point. When the fixation point disappears, a picture will appear. Please imagine yourself in the picture and fully experience the emotion the scene evokes. After the picture disappears, please evaluate your emotional intensity at this time based on the instructions provided.”

##### Cognitive reappraisal-task (emotion downregulation)

The participants will be instructed to weaken their emotions while viewing stimulus pictures and rate their emotional arousal after each picture. The following instructions will be provided at the beginning of the task: “When a fixation point ‘ + ’ appears in the center of the screen, please keep your eyes on the fixation point. When the fixation point disappears, a picture will appear. Please keep an objective attitude and try not to feel any emotion from the picture. After the picture disappears, please evaluate your emotional intensity at this time based on the instructions provided” (Figure 3).

**FIGURE 3 F3:**
[figure not shown]
Schematic diagram of a computerized CR task. Adapted from https://699pic.com/.

The emotional regulation effectiveness of CR can be calculated by subtracting the emotional intensity for the simple viewing task from that for the CR + task or CR- task. The upregulation effect (arousal_*CR*+_ - arousal_*baseline*_) and the downregulation effect (arousal_*baseline*_ - arousal_*CR*–_) can be obtained before (T_0_) and after (T_1_) CR training while MRI is performed (T_0_ and T_1_).

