On the other hand, the frequent user of CR showed stronger downregulation of amygdala activation to negative emotion stimuli (Kanske et al., 2012), and CR in healthy individuals can attenuate the excitatory connectivity from the dlPFC to the inferior frontal gyrus (IFG) and increase the inhibitory connectivity from the IFG to the dlPFC, which supports the selection of appropriate alternative CR strategies (reinterpretations) in the IFG, and afterward, inhibition of original interpretations maintained and monitored in the dlPFC (Morawetz et al., 2016). Neurofeedback-guided CR training targeting the left vlPFC improved the frequency of CR strategy use (indexed with ERQ) as well as depression symptoms (Keller et al., 2021). Therefore, CR training may enhance CR ability by changing the functional activity/connectivity pattern of prefrontal-amygdala circuits, which then alleviates cognitive biases and thus depressive symptoms.

Researchers suggested that specific measures using lab-based tasks may be more sensitive to detect training effects (Cohen and Ochsner, 2018). Therefore, in this study, we will combine the RIT, CR training, and fMRI, as well as self-report measures (cognitive/emotion/symptoms) to address the following aims: (1) to examine whether the CR ability (reappraisal inventiveness) of the population with cognitive vulnerability to depression is abnormal; (2) to test the hypothesis that CR training alleviates depressive symptoms through the mediators of cognitive bias (e.g., interpretation bias and/or rumination bias); (3) to investigate the neural substrates (structural/functional) of prefrontal–amygdala circuits through which CR training improves the ability to generate a CR strategy; and (4) to examine the short- and/or long-term effects of CR training on reducing depression symptoms in cognitively vulnerable individuals immediately after intervention and/or 6 months to provide theoretical and practical evidence for early intervention in these populations. We postulate that CR training improves CR ability (RIT) by changing the brain activity/function connectivity of the prefrontal-amygdala circuits, thereby reducing negative cognitive biases (NCPBQ-NIB, NCPBQ-NRB, and CSQ) and improving depression symptoms (CESD) (Figure 1).

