##### Data analysis

(1) Analysis of the morphological characteristics of brain structure: Voxel-based morphometry (VBM) will be adopted to calculate the concentration and volume of each voxel in different brain tissues (gray matter, white matter, and cerebrospinal fluid) using templates for the whole brain and different brain tissues created based on 3D data, and the volumes of ROIs will be compared between different groups to examine (1) whether the volumes of ROIs before and after CR training differ significantly and (2) if the volumes of ROIs differ significantly, whether the changes in the volumes of the ROIs can predict depressive symptoms immediately after training (T_1_) or 6 months later (T_2_).

(2) Region of interest analysis: The anatomical localization of functional images will be determined with reference to the anatomical maps of the brain in Talairach coordinates and based on the opinions of experienced neuroimagers. Using MARSbar software, the prefrontal subregions (dlPFC/dmPFC/vlPFC/vmPFC) and the amygdala will be extracted as BOLD signals of ROIs by subtraction between the baseline and CR (±) conditions. The data will then be exported to SPSS for statistical processing, in which the activation of the region of interest will be used as a predictor of depressive symptom scores to investigate (1) whether the activation levels of regions of interest (prefrontal lobe and the amygdala and its subregions) before and after CR training differ significantly and (2) if the activation levels do differ significantly, whether the changes in the activation levels of the regions of interest can predict depressive symptoms (T_1_ and T_2_).

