## Discussion

CR is one of the key components of CBT, and accumulating evidence suggests that CR training as a standalone treatment is effective for depressed patients to improve negative effects and enhance wellbeing (Berking et al., 2013; Ehret et al., 2014; Weytens et al., 2014). Prior studies found that individuals with cognitive vulnerability are at high risk for depression, which merits attention considering the prevalence of depression. Nonetheless, as a highly accessible and cost-effective intervention, the mood-lifting effects of CR for cognitively vulnerable individuals are unknown. Therefore, the current study could provide support for the potential of CR training for the prevention of depression in vulnerable groups. Of note, with the progress of e-mental health, CR training is promising to be developed into a cost-effective computerized program that is easy to implement for counselors and is suitable for early interventions of cognitively vulnerable individuals to depression.

Furthermore, despite ample evidence for the role of the prefrontal–amygdala circuit in CR, as well as prefrontal–amygdala dysfunction in CR deficits in patients with depression, the impact of CR training on hypothesized neural targets remains unclear, especially the cause–effect relationship between these regions during CR training. Based on previous evidence, we propose that CR training may involve increased top-down cognitive control areas (such as dlPFC, vlPFC, and dmPFC) and reduced bottom-up emotion responding areas (such as vmPFC and amygdala), as well as strengthened interactions between the PFC and the subcortical regions (mainly the amygdala). In addition, the hypothesis about the changes after CR training is exploratory and without strong *a priori* evidence; however, the structural changes of CR training may be of clinical significance. The current study aims to reveal the neural substrates of CR training, which remain largely unknown yet and have the potential to inform techniques, such as real-time fMRI neurofeedback (Zweerings et al., 2020; Keller et al., 2021), to precisely impact the neural targets underlying CR and amplify the effects of CR training.

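### Regulation scores and ROI activation at T1 are measured against a viewing condition that training may itself change, so neither can be read without the viewing result

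*Protocol article*

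**What the plan says.** The section on the CR task defines what baseline means: "The CR task for each participant will include 3 conditions: simple viewing (baseline), CR + (emotion upregulation), and CR- (emotion downregulation"). It is a task condition that opens each run of the task, not the pretraining visit. The viewing instruction asks participants to look at the pictures naturally and rate their arousal.

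The text with Figure 3 then gives the score: "The emotional regulation effectiveness of CR can be calculated by subtracting the emotional intensity for the simple viewing task from that for the CR" conditions. Its formulae are CR+ minus viewing for upregulation and viewing minus CR- for downregulation, and these "can be obtained before (T_0_) and after (T_1_) CR training while MRI is performed (T_0_ and T_1"). The T1 score therefore uses T1 viewing.

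For imaging, item (2) of the neuroimaging Data analysis section says that the prefrontal subregions and the amygdala "will be extracted as BOLD signals of ROIs by subtraction between the baseline and CR (±) conditions". The same item asks first whether activation differs significantly before and after training. Only if it does are the activation changes used to predict depressive symptoms.

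On mechanism, the Discussion proposes that training may involve "reduced bottom-up emotion responding areas (such as vmPFC and amygdala"). The Introduction cites evidence that "the frequent user of CR showed stronger downregulation of amygdala activation to negative emotion stimuli".

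**The concern.** The reference for the T1 score is measured after randomisation, in participants who may by then have had eight training sessions. Nothing in the viewing instruction stops a trained participant from regulating while viewing. The protocol's model places the emotional response that training should dampen in vmPFC and amygdala, and those regions also respond during plain viewing. If training changes the viewing response, a score built as a difference from viewing mixes two effects: the change under instruction and the change in the reference.

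The mechanistic aim is at stake. A real reduction in emotional reactivity could appear as a smaller downregulation gain, as none, or as a worsening, and at the same time as an upregulation gain. In the ROI analysis, a fall of similar size in both conditions would leave the contrast unchanged. The significance condition would then also stop the prediction analysis. The article fixes the scoring rule, but names no comparison of the viewing condition between the intervention (CR) and waiting-list (WC) subgroups that would show which of these had happened.

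**Working it through.** **Plan's own figure.** There is none for this index. The stated sample size (75 per group, d printed as 0.0.39, 65% power) rests on changes in HRSD/BDI-II, which are depression scores. It says nothing about the power of an arousal or BOLD difference, so no power figure is derived here.

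**Inputs.** The two formulae and the T0/T1 timing come from the text with Figure 3. The meaning of baseline comes from the Task section. The 1-9 rating scale comes from the training procedure. All changes in ratings below are assumptions.

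**Algebra.** Let V, D and U be the mean response under viewing, CR- and CR+. Let training, relative to the waiting list, lower V by s and D by c, and change U by u.

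- Down = V - D. Effect of training = (-s) - (-c) = c - s.
- Up = U - V. Effect of training = u - (-s) = u + s.
- Down + Up = U - D, so viewing cancels in the sum. A fall in viewing moves credit from the downregulation index to the upregulation index.

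Share of the CR- gain that the downregulation index shows, (c - s)/c:

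- s/c = 0.25: 75%
- s/c = 0.5: 50%
- s/c = 1: 0%
- s/c > 1: negative, scored as worse regulation

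**Illustration on the 1-9 scale.** Assume T0 means of viewing 6.0, CR- 4.0 and CR+ 7.5. Then Down = 6.0 - 4.0 = 2.0 and Up = 7.5 - 6.0 = 1.5. At T1, CR- has fallen by 1.0 to 3.0, CR+ is unchanged, and the waiting list does not change.

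| Fall in viewing | T1 viewing | T1 Down (change) | T1 Up (change) |
|---|---|---|---|
| 0 | 6.0 | 3.0 (+1.0) | 1.5 (0) |
| 0.5 | 5.5 | 2.5 (+0.5) | 2.0 (+0.5) |
| 1.0 | 5.0 | 2.0 (0) | 2.5 (+1.0) |
| 1.5 | 4.5 | 1.5 (-0.5) | 3.0 (+1.5) |

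The response under CR- is the same in every row. Only the reference moves.

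**Carry-over in the other direction.** If viewing and CR+ both rise by 0.5, the upregulation index changes by 0.5 - 0.5 = 0. With CR- unchanged, the downregulation index rises by 0.5.

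**ROI signal.** The same algebra holds with BOLD in place of ratings. If amygdala response falls equally under CR- and under viewing, the contrast does not change.

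**The case against.** The strongest reply is that the contrast is the construct. The Introduction defines reappraisal effectiveness as the response under instruction relative to passive viewing, and a same-session reference removes habituation and drift in use of the rating scale. Scoring T1 against T0 viewing would bring those shifts back in. This stands, and it is why the contrast should be kept.

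Carry-over is also an inference. The Discussion says only that training may reduce vmPFC and amygdala activity, without saying in which task condition. The cited amygdala evidence concerns habitual users of reappraisal, not trained participants who are viewing. Training practises upregulation as well as downregulation, on positive and negative pictures, so even the direction is open. This stands too. It limits the point to what training may do to viewing.

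The rating index is neither a primary nor a listed secondary outcome, and an article need not give every reporting detail. That lowers the stakes. But the scoring rule and the condition on the ROI prediction analysis are stated here, and they serve a stated aim.

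A reader might go further and infer that all carry-over is scored as no benefit. The formulae do not support that: calmer viewing raises the upregulation score, and for downregulation a null result is only the case s = c. A reader might also turn an assumed halving of the effect into a loss of power by using d = 0.39. That effect size comes from depression scores and cannot be carried over to this index.

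**Conclusion.** The point holds for the rating indices and for ROI activation. Both are referenced at T1 to a post-randomisation condition that training may change. A fall in the viewing response is taken one for one from the downregulation score and added one for one to the upregulation score. Neither can be interpreted alone, and a general fall in amygdala or vmPFC reactivity could escape the ROI contrast and shut off the prediction analysis that depends on it.

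The algebra is exact. The amount of carry-over is unknown, and the ratios and ratings shown are assumptions.

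It would be wrong to conclude that the main efficacy result is at risk. CESD, NCPBQ, CSQ, RIT and ERQ do not use this subtraction, and the volume and connectivity analyses are not described as using it. This is a worthwhile and inexpensive improvement to the mechanistic aim, and not a flaw in the primary comparison.

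**What to change.** - Keep the within-session contrast as the effectiveness index.
- State that viewing-condition ratings will be compared CR v WC at T1 with the T0 value as covariate. Do the same for the viewing ROI response if the scanner task has a usable fixation or rest baseline.
- Report viewing, CR+ and CR- means by arm and time, preferably also by picture valence.
- Interpret the difference scores only together with the viewing result.
- Do not make the ROI symptom-prediction analysis conditional on significance of the difference contrast alone.

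The cost is mainly analysis wording. Viewing ratings are already collected, and both subgroups are scanned before and after training. There is one extra contrast per measure. Viewing against fixation is a noisier BOLD estimate, and the visible text does not confirm that the scanner task supports it: the only fixation described is a 2 s cue before each picture in the training trials. If there is no such baseline, the addition is limited to the ratings, and the ROI result should carry that caveat.

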#### Training procedure

The training includes 8 sessions (2 sessions/week) within 4 weeks. Each session is divided into 9 blocks (20 trials/block, 180 trials in total). The order of the experimental content is counterbalanced, i.e., in each block, one-half of the subjects start with a CR + task and the other half start with a CR- task. In each session, pictures with different valences are randomly presented in trials. Each trial lasts 18–21 s: first, a fixation point is presented for 2 s at the center of the screen which the participant fixes; then, a positive or negative emotion picture is presented on the screen and the subject is asked to focus on the emotion picture for 8 s to allow emotional arousal. After the picture disappears, the subject is asked to report his/her emotional intensity at the moment on a 1–9 scale within 4–7 s, during which the subject’s reaction time of key press is recorded. If the subject does not press the key in the allotted time, the interface screen will continue (Figure 4).

**FIGURE 4 F4:**

CR training process: one session as an example (4 weeks, 2 sessions/week).

After the experiment, the subject is asked about his/her conformity to the instructions (manipulation check). Both the quantitative and qualitative CR manipulation checks will be conducted by the experimenter to confirm that they obeyed CR training instructions (Rood et al., 2012). After each block, participants briefly state the content coming into mind during that block (recorded by the experimenter after the informed written consent by the participants) and the degree to which they reappraise the emotional pictures during that block on a 0–100 rating scale.

### Primary outcome

The structured clinical interview for DSM-IV-TR Axis Disorders (SCID-I) will be used to diagnose and screen for major depressive disorders and exclude other DSM-IV axis I mental disorders when recruiting subjects. Demographic information, including gender, age, ethnicity, education, and duration of illness (months), will be collected using a questionnaire.

#### Center for epidemiologic studies depression scale

The center for epidemiologic studies depression scale (CESD) will be used by subjects to self-evaluate their current depressive symptoms (within a week), focusing on depressive emotions or mood rather than somatic symptoms. Subjects with depressive symptoms will undergo preliminary screening to facilitate further diagnosis. The scale contains 20 items in 4 dimensions (negative emotions, positive emotions, physical symptoms, and interpersonal relationships) that are scored on a 4-level scale (“no or rarely, less than once a day,” “sometimes or only a small part of the time in 1 day,” “frequently or half of the time in 1 day,” and “most of the time or all the time in 1 day”); the higher the score is, the more severe the level of depression.

### Secondary outcomes

#### Negative cognitive bias

##### Cognitive style questionnaire

The CSQ will be used to screen subjects in the group of individuals cognitively vulnerable to depression and the group of individuals not cognitively vulnerable to depression. The CSQ was developed based on the hopelessness theory and was designed to be used to assess an individual’s negative cognitive styles, mainly including the individual’s perceptions of the causes, consequences, and self-worth after an event. The Chinese-translated version of the CSQ has good internal reliability (Cronbach’s alpha coefficient = 0.94), satisfactory 8-week test–retest reliability (reliability = 0.59), and good construct validity for the four-factor model (CFI = 0.91, RMSEA = 0.09), which included general-local causes, stable-temporary causes, consequences, and self-worth (Chen et al., 2014).

##### Negative cognitive processing bias questionnaire

The negative cognitive processing bias questionnaire (NCPBQ) contains 4 dimensions, i.e., negative attention bias (NAB), negative memory bias (NMB), negative interpretation bias (NIB), and negative rumination bias (NRB), using a Likert 4-point scale from 1 (completely disagree) to 4 (completely agree). The NCPBQ has good internal reliability (Cronbach’s alpha coefficient = 0.89), split-half reliability (*r* = 0.87), construct validity for a four-factor model that explained 50.152% of the total variation (CFI = 0.92, RMSEA = 0.05), and criterion validity coefficients of 0.395 (relative to the Beck Depression Self-Rating Scale) and 0.548 (relative to the Dysfunctional Attitude Questionnaire) (Yan et al., 2017). The negative interpretation bias (NIB) and the negative rumination bias (NRB) subscales will be utilized in the mediation analyses.

#### Reappraisal ability/tendency

##### Reappraisal inventiveness test

RIT includes 4 scenes that can trigger emotions. Participants are asked to imagine themselves in the scene as vividly as possible within a specified time (3 min), after which they are asked to think of reappraisals that can change the induced emotion within 20 s and then record the reappraisals in 3 min. RIT was scored on two scales: (a) RIT-fluency was indicated by the number of reappraisals generated and (b) RIT-flexibility was indicated by the number of categories of different reappraisals (Weber et al., 2013). To improve the internal validity of the test, we set the induced emotions to sad and happy. Before the test, the subjects will be given examples to illustrate how to generate as many reappraisals as possible for a given emotional stimulus so that they can transfer to the formal test.

